## Outcome measures

### Primary outcome

Maternal cardiac dysfunction or remodeling in the first and third trimesters of pregnancy and 12 months postpartum, defined as any of the following:Abnormal cardiac performance in echocardiographic assessments.Abnormal concentrations of cardiac biomarkers (Copeptin, hs-cTnT, NT-proBNP).

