#### Database development and statistical analysis

A web-based database will be developed through a restricted website. All variables will be recorded, and the collected data will be coded and processed with adequate precautions to ensure patient confidentiality. Each participating physician will receive a login name and password to gain access to the web-secured database, with access restricted to clinicians with electronic password.

Once sample collection and laboratory determinations of biomarkers are finished, we will proceed to evaluation and analysis of the results obtained with the aid of the Statistics Department at our institution. Measures will be normalized to expected values for the respective gestational age. For biomarker measurements without reference values in pregnancy, we will obtain reference values from the control population, estimated by linear modeling and describe as multiples of the median (MoM). Variables not following a Gaussian distribution will be log-transformed for analysis.

For the primary outcome, differences in all registered variables among the three study groups will be evaluated at the three evaluation points. Group comparisons will be performed by analysis of variance (ANOVA), followed by post-hoc tests or Chi-squared tests for proportions. Associations and confusion variables will be explored by a multivariate approach, using logistic regression models.

For secondary outcomes, descriptive data will be analyzed at all relevant time-points, frequency of altered values registered and compared among groups and times. Correlations between biochemical markers, including angiogenic imbalance, and cardiac dysfunction/remodeling will be assessed. Diagnostic test parameters (sensitivity, specificity, positive and negative predictive values) will be calculated, and Cox proportional-hazards model will be performed. Univariate and multivariate analysis will allow identifying which variables can be incorporated to a multivariable model to predict CV risk or disease in PE.

In all analyses, a *p* value below 0.05 will be considered statistically significant. Data will be analyzed using the IBM SPSS Statistics 23 statistical package.

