The association between CVD and angiogenic factors has been investigated in non-pregnant populations. Increased concentrations of PlGF at admission are associated with worse outcomes in acute coronary syndromes, although PlGF stimulates angiogenesis and mediates recovery of cardiac pathologies [34]. Increased sFlt-1 concentrations are related to acute coronary occlusion and poor cardiac function in patients with stable coronary disease [35], and with development of endothelial vascular dysfunction, myocardial injury and adverse CV outcomes in patients with congestive heart failure [35]. As in PE, the use of the sFlt-1/PlGF ratio appears to be more predictive of adverse outcomes in coronary artery disease than either biomarker alone [36]. Finally, although angiogenic factors are critical players in PE endothelial dysfunction, there is no evidence supporting their role as maternal cardiotoxic factors, and CV risk later in life. A possible explanation could be that maternal cardiac damage in PE is so subtle that it cannot be detected by current imaging techniques; therefore, the use of cardiac biomarkers may have a role for early detection.

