There are potential limitations and considerations of the present project. We would only observe subclinical CV changes due to the short length of postpartum follow-up (12 months). Clinically evident CV outcomes will probably require much longer follow-up given that the studied population will only include young, pregnant women. However, our aim is to initiate a cohort study of patients with high-risk for PE or that develop the disease, in order to adequately follow-up in the long-term, as we have previously done with other cohorts. Development of a predictive model of future CVD risk or complications, including clinical and echocardiographic variables, CV and placental biomarkers, will require further validation in prospective well-powered studies. Finally, in our study we will assess associations between CV findings and angiogenic factors but finding of potential causal links between both will still require further studies.

To conclude, this study will provide, for the first time, evidence characterizing the association between angiogenic imbalance and CV dysfunction/remodeling in women at risk for or developing PE and, in their offspring, both during and after pregnancy. We expect to provide data supporting the association between abnormal angiogenesis and CV dysfunction/remodeling during pregnancy and fetal life, therefore identifying new therapeutic targets for future studies aiming to prevent CV morbidity associated with PE. The goal of this research is to obtain insight in the particular risk factors that link pregnancy and CV health, and thus, reduce the burden of the disease.

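### The only confounder-adjusted method named for the primary outcome is logistic regression, most naturally on the abnormal yes/no flag, while the continuous values prepared for analysis get only unadjusted ANOVA

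*Protocol article*

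**What the plan says.** Under Primary outcome, the article sets a yes/no endpoint: "Maternal cardiac dysfunction or remodeling in the first and third trimesters of pregnancy and 12 months postpartum, defined as any of the following". The two components are abnormal echocardiographic performance and "Abnormal concentrations of cardiac biomarkers (Copeptin, hs-cTnT, NT-proBNP").

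Under Database development and statistical analysis, measures are normalised for gestational age or expressed as multiples of the median, and "Variables not following a Gaussian distribution will be log-transformed for analysis". Two methods are then given for the primary outcome:

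- "Group comparisons will be performed by analysis of variance (ANOVA), followed by post-hoc tests or Chi-squared tests for proportions". No covariates are named.
- "Associations and confusion variables will be explored by a multivariate approach, using logistic regression models". Neither the response nor the covariates are named.

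The relation with angiogenic markers on a continuous scale appears only among the secondary analyses: "Correlations between biochemical markers, including angiogenic imbalance, and cardiac dysfunction/remodeling will be assessed". No adjustment is attached to it.

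On the size of effect, the Discussion says "We would only observe subclinical CV changes due to the short length of postpartum follow-up (12 months"). It also offers, as one possible reason for the lack of earlier evidence, "A possible explanation could be that maternal cardiac damage in PE is so subtle that it cannot be detected by current imaging techniques".

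**The concern.** This is an observational cohort. The high-risk group is selected on maternal risk factors, blood pressure, PAPP-A and uterine artery Doppler (Inclusion criteria). The primary aim is the relation between angiogenic environment and maternal cardiac dysfunction. An unadjusted group comparison mixes that relation with the selection factors, so an adjusted analysis is needed to interpret it.

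The only adjusted method named for the primary outcome needs a binary response. If that response is the abnormal flag, two women on the same side of a limit count as identical however far apart their values are. Small shifts within the normal range, which are what the Discussion anticipates, are what an abnormality limit detects worst. At stake is a confounder-adjusted null result that reflects the scale and not the biology.

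**Working it through.** The article's only sample-size figure is the total, and it adds up: 280 + 100 + 60 = 440. No power, effect size, standard deviation, abnormality rate or cut-off is attached to it, so there is no power figure to reproduce.

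**Inputs from the document**
- PE cases: 40 expected in the high-risk group + 60 with established PE = 100. Controls: 100.
- Loss: 10%, giving 90 vs 90, or 36 vs 90 if only the high-risk women who develop PE are counted. The established-PE women enter at diagnosis, so the smaller contrast is the one available in the first trimester.
- The article says the 10% is already included. Using 100 vs 100 instead does not change the picture (last bullet under Cross-checks).
- Significance level 0.05, taken as two-sided because sidedness is not stated.

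**Assumptions**
- Normally distributed marker with SD 1, and a shift *d* that gives 80% power for the t-test on the full scale: *d* = 0.42 for 90 vs 90 and 0.56 for 36 vs 90.
- Abnormal means above control percentile *q*.

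**Formulas**
- p0 = 1 − q and p1 = 1 − Φ(z_q − d)
- p̄ = (n1·p1 + n0·p0)/(n1 + n0)
- s0 = √[p̄(1 − p̄)(1/n1 + 1/n0)]
- s1 = √[p1(1 − p1)/n1 + p0(1 − p0)/n0]
- Power = Φ[(p1 − p0 − 1.96·s0)/s1]

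**Single marker, 90 vs 90, d = 0.42**

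| Cut | p0 | p1 | s0 | s1 | Power |
|---|---|---|---|---|---|
| none (continuous) | – | – | – | – | 80% |
| 80th | 0.20 | 0.337 | 0.0661 | 0.0653 | 54% |
| 90th | 0.10 | 0.194 | 0.0528 | 0.0523 | 43% |
| 95th | 0.05 | 0.110 | 0.0405 | 0.0402 | 32% |

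Simulation of the chi-squared test gives 55–56% at the 80th percentile and the same values at the other two. For 36 vs 90 with *d* = 0.56, the results are about 58%, 51% and 42%.

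**Cross-checks**
- With one confounder adjusted for in both models (1,000 runs, 90 vs 90, shift 0.4 SD), linear power is 78–82%. Logistic power is 44% (90th) or 31% (95th).
- With a continuous angiogenic exposure (0.15 SD per SD, n = 440 × 0.9 = 396), adjusted linear power is 88–90%. Logistic power is 40% or 32%.
- With 100 vs 100 and a shift of 0.4 SD, power is 81% continuous against 55%, 43% and 32%.

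**The composite as defined**

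A single cut is not the stated endpoint, so the any-of rule was simulated: 90 vs 90, *d* = 0.42, correlation 0.3 between markers, each cut at its 95th percentile.

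| Pattern | Composite flag | Continuous mean of the same markers |
|---|---|---|
| 3 to 8 markers, all shift | about 62–84% | 97% or more |
| 3 to 8 markers, one shifts | about 8–15% | about 9–24% |

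If only one marker moves, averaging is little help either. The 80% is kept only by analysing that marker on its own continuous scale.

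**The case against.** **The logistic response is not stated.** It could be PE status, which is also binary, with continuous markers and confounders as predictors. Nothing would then be dichotomised. Simulated at the same sizes, that model matches the adjusted linear one (81% vs 80% for both 90 vs 90 and 36 vs 90). This stands as a possibility. However, the primary aim has cardiac dysfunction as the outcome and the primary outcome is a flag, so the flag is the more natural response. If PE status were meant, no adjusted model of the cardiac outcome would be named at all.

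**The article is condensed.** Model details may be in the full protocol or analysis plan, and the secondary analyses mention multivariable modelling without naming a type. So one cannot say that adjusted linear models are excluded. The point is about the method the article does name.

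**Continuous values are analysed.** ANOVA and the correlations would both respond to a shift within the normal range. A reader might infer that such a shift would be reported as no association. The text does not support that. What is missing on that scale is adjustment. The logistic step is also described as exploratory, so the text does not itself make it decisive.

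**The composite is not one marker.** A reader might carry the 32% over to the primary outcome, or expect too few events for adjustment. Neither follows. With three to eight markers, the control event rate is about 13–27%, and power is moderate if all of them shift. Sparse events concern single-marker flags: about 26 or 14 in total at the 90th or 95th percentile, 90 vs 90.

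**More models mean more tests.** This stands and limits the fix.

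**Conclusion.** The point holds in a limited form. For the primary outcome, the article names continuous analysis only without adjustment, and adjusted analysis only by logistic regression, most naturally on the abnormal flag. On that reading the adjusted association is estimated on a scale poorly matched to the subclinical change the authors expect.

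For one marker, the illustrated loss is about 24 to 48 percentage points from 80% (90 vs 90, cuts from the 80th to the 95th percentile). For the composite, it ranges from little or none when many markers shift together to nearly all of the power when only one does. These sizes rest on assumed normality, shifts, cut-offs, correlation and shift pattern, because the article gives none of them. That every adjusted estimate must be dichotomised is an inference from the outcome definition and not something the text states.

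**What to change.** Under Database development and statistical analysis:

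1. Add a confounder-adjusted linear model (ANCOVA) on the normalised or log-MoM value as the main adjusted analysis. Apply it to a short, pre-named list of key echocardiographic parameters and the three cardiac biomarkers, with the confounders intended for the logistic model.
2. Use ordinal or censored regression for any marker often below its detection limit.
3. Keep logistic regression on the abnormal outcome as the clinically readable summary, and state its response.

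The cost is a few sentences. No new data are needed and the transformed values are already planned. Results would appear as mean differences or ratios as well as odds ratios.

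The real price is more tests over three visits, so the list must be short or multiplicity controlled. As an illustration, take six markers at one visit with a Bonferroni level of 0.05/6 = 0.0083 (critical value 2.64). A marker with 80% power at 0.05 (1.96 + 0.84 = 2.80) keeps Φ(2.80 − 2.64) = Φ(0.16), about 56%. That is still above the uncorrected 43% and 32% for a flag cut at the 90th or 95th percentile, but it shows why the list should not cover every recorded parameter.

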### Inclusion criteria

Women between 18 and 45 years of age, with singleton pregnancies and high-risk for PE according to our first trimester screening protocol [24], which includes registration/measurement of maternal risk factors, blood pressure (BP), pregnancy-associated plasma protein A (PAPP-A) and mean uterine artery pulsatility index (UtA-PI), at 11^+ 0^ to 13^+ 6^ weeks of gestation. The estimated sample size for the high-risk group is 280 patients, who will be divided according to the subsequent development of PE:True PE: women from the high-risk group who develop PE (estimated *n* = 40)False PE: women from the high-risk group who do not develop PE (estimated *n* = 240)

An additional group of healthy pregnant women with first trimester low-risk screening for PE will be recruited (*n* = 100).

Additionally, women with established diagnosis of PE (*n* = 60) that were not participating previously in the study, will be included at time of diagnosis. The local research coordinator and/or staff will identify eligible women, invite them to participate, provide written and oral information, and obtain the written informed consent.

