### Secondary outcomes

Cardiac dysfunction or remodeling in fetuses from mothers at risk for PE or established PE, defined as abnormal cardiac performance in third trimester echocardiographic ultrasound assessment and/or abnormal cardiac biochemical profile (Copeptin, NT-proBNP, hs-cTnT) in umbilical cord blood at delivery.Abnormal BP or lipid profile in the PE group as compared to the others, in the first, third trimester of pregnancy, or at 12 months after delivery.Development of a combined model for prediction of PE, including biochemical and biophysical markers of CV and placental dysfunction.Cardiac and metabolic status at 12 months after delivery and their correlation with cardiac and PE risk variables obtained during pregnancy. Development of a combined model for prediction of CV risk 12 months after delivery, including biochemical and biophysical markers of CV and placental dysfunction.

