## Statistical analysis

### Sample size

We have planned a 3 year-period recruitment, considering the number of deliveries at our institution. To obtain an adequate sample, a total of 2800 screenings must be performed, assuming there is a 1-to-6 ratio between high-risk cases vs controls. We will include all pregnant women attending our center for first trimester screening and agreeing to participate in the study. They will be divided into two groups according to their PE risk; we plan to include 280 pregnancies with high-risk of PE and 100 patients with low-risk of PE, as well as 60 patients with established PE; we have included an estimated 10% drop-rate during the study. The study has already begun the enrollment; as of 30/09/2021 110 high-risk PE patients, 54 low-risk PE patients and 10 established PE patients have been included.

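### Choosing predictors by significance testing on the fitting data, with few events and roughly 25–40 candidates, will give optimistic prediction models unless the optimism is corrected

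*Protocol article*

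**What the plan says.** Two prediction models appear under Secondary outcomes in the protocol article. One predicts PE. The other is described as "Development of a combined model for prediction of CV risk 12 months after delivery, including biochemical and biophysical markers of CV and placental dysfunction". Secondary aims describes the CV model as one for women with PE.

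The method is in Database development and statistical analysis: "Univariate and multivariate analysis will allow identifying which variables can be incorporated to a multivariable model to predict CV risk or disease in PE". The same section sets p<0.05 for all analyses. That sentence names the CV model, and the article gives no separate selection method for the PE model.

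On numbers, Sample size states that "we plan to include 280 pregnancies with high-risk of PE and 100 patients with low-risk of PE, as well as 60 patients with established PE", and adds that "we have included an estimated 10% drop-rate during the study". Inclusion criteria splits the 280 high-risk women into an estimated 40 who develop PE and 240 who do not. The 60 women with established PE enter at diagnosis.

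On candidates, the Discussion intends to use all the information from the biomarkers, together with clinical and echocardiographic variables, for a CV risk score. It also says that a predictive model of future CVD risk "will require further validation in prospective well-powered studies".

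**The concern.** When the same women are used to screen many candidates by p-value, to estimate the coefficients and to measure performance, chance associations that pass the threshold are kept and count as predictive ability. The apparent AUC is then too high and the coefficients too extreme. Both effects grow as events per candidate fall, and here that ratio is low for both models.

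At stake are two secondary outcomes and one secondary aim. A combined risk score could be reported as more useful than it is, and its predicted risks would be too spread out in new patients. The primary outcome is not affected.

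**Working it through.** **Events for the PE model.** The plan's own figure is 40 events. It is reproduced by 280/(1+6) = 40, and 40 + 240 = 280. This needs the 1-to-6 ratio in Sample size to be read as PE versus no PE within the high-risk group, although the text describes it as "assuming there is a 1-to-6 ratio between high-risk cases vs controls". Taking off the 10% drop-out gives 40 × 0.9 = 36 events in 280 × 0.9 = 252 women. The 60 women enrolled at diagnosis have no first-trimester measurements, so they cannot add events to a first-trimester model.

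**Base for the CV model in PE.** 40 + 60 = 100 women, or 100 × 0.9 = 90 after drop-out. The number with an abnormal outcome at 12 months is not stated; 20 and 30 are assumed below.

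**Candidates at one visit (counted from the Methods).** About 16 maternal echocardiographic parameters, 5 biomarkers and 3 screening measures (BP, PAPP-A, UtA-PI) make 24. Maternal history adds to this. The 24-h BP monitoring adds at least 8 (24 + 8 = 32), and more if day and night values are counted separately. Roughly 25–40 is a fair range.

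**Events per candidate.** With 36 events: 36/20 = 1.8, 36/30 = 1.2, 36/40 = 0.9. With 40 events: 2.0, 1.3, 1.0.

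**Candidate parameters the PE sample supports.** The criterion is expected shrinkage S of at least 0.9: p = n × (S − 1) × ln(1 − R²/S), where R² is the Cox–Snell value. At an event proportion of 36/252 its maximum is 0.560. The Nagelkerke values are assumptions.

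| Nagelkerke R² (assumed) | Cox–Snell R² | Parameters supported, n = 252 | Women needed for 30 candidates |
|---|---|---|---|
| 0.15 | 0.084 | 2.5 | 3064 |
| 0.30 | 0.168 | 5.2 | 1453 |
| 0.50 | 0.280 | 9.4 | 806 |

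**Simulated optimism.** Each data set was screened by t-test at p<0.05, followed by backward logistic elimination at p<0.05, with 300 runs per scenario. True AUC was measured in a new sample of 14,000. The PE-model rows use 36 events in 252 women, 20, 30 or 40 candidates, and predictor correlation 0 or 0.3. The last four rows use 30 candidates, two predictors of 0.5 SD and correlation 0.3. Effects and correlations are assumed throughout.

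| Scenario | Apparent AUC | True AUC | Excess | Calibration slope |
|---|---|---|---|---|
| PE model, no real predictor | 0.57–0.64 | 0.50 | 0.07–0.14 | about 0 |
| PE model, two predictors of 0.5 SD | 0.69–0.73 | 0.63–0.65 | 0.05–0.09 | 0.59–0.74 |
| PE model, four predictors of 0.4–0.7 SD | 0.76–0.82 | 0.72–0.77 | 0.04–0.06 | 0.72–0.82 |
| PE model, 40 events in 280 | 0.70 | 0.64 | 0.06 | 0.70 |
| CV model, 20 events in 90 | 0.70 | 0.58 | 0.12 | 0.36 |
| CV model, 30 events in 90 | 0.70 | 0.60 | 0.10 | 0.48 |
| Third-trimester PE model pooling established PE, 96 events in 442 | 0.70 | 0.66 | 0.03 | 0.84 |

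The 442 in the last row is approximate and slightly exceeds the planned total of 440. Repeating that row with 100 events in 440 and with 90 in 396 (both less 10%) gave an excess of 0.02 and 0.04, so about 0.03 is a fair summary.

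**The case against.** The strongest reply is that this is a condensed article. It does not say that no shrinkage or internal validation will be done; it is silent, and a full protocol or SAP may provide for both. That stands. A reader might infer that uncorrected performance is certain to be reported, but the article does not support that. The point rests on the selection method the article does state, which suits this sample poorly whatever is added later.

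Several further objections stand in part:

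- The quoted sentence concerns the CV model, while the 36–40 events belong to the PE model. The two must be kept apart. Doing so does not help the plan, because the CV model has the smaller base and the larger assumed optimism. If it were built in all women followed to 12 months rather than in those with PE, the base would be larger, but the event count would still be unstated.
- The sentence fixes neither the order of the steps nor an entry rule. Univariate screening followed by multivariable fitting at p<0.05 is the natural reading, not an explicit rule. Looser screening would give larger excesses, but the article mentions no threshold other than 0.05.
- The count of 36 is derived; the article states 40. Some drop-out may occur after PE status is known, and low-risk women could add a few cases. With 40 events the result hardly changes.
- The article does not say that every recorded measure will be a candidate, and the text on visits does not place 24-h BP monitoring in the first trimester. Even 20 candidates leave only about 2 events each.
- The no-predictor scenario is pessimistic, since the Background cites evidence for several of these markers.

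The Discussion does acknowledge the need for later validation, but only for the CVD-risk model. Validation in other studies does not change the AUC and coefficients published from this one.

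**Conclusion.** The concern holds in a limited form. Significance-based selection with about 1–2 events per candidate will give an optimistic PE model: an AUC excess of about 0.04–0.09 with real predictors, 0.07–0.14 with none. The CV model in PE is probably worse, at about 0.10–0.12 if 20–30 of 90 women have the outcome. These sizes depend on assumed effects, correlations, candidate numbers and CV event counts, and on apparent performance being reported without correction.

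A reader might conclude that every model from this study will be strongly over-optimistic. That is too strong: with four stronger predictors the excess is 0.04–0.06, and a third-trimester PE model pooling the established cases would show only about 0.03. This is a cheap improvement to two secondary analyses and does not threaten the primary result.

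**What to change.** In Database development and statistical analysis, replace selection by univariate and multivariate testing with one of two methods, stated separately for the PE model and the CV model:

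1. A small candidate set fixed in advance and sized to each model's expected events. For the PE model the criterion above supports about 2.5 to 9.4 parameters, depending on the assumed R². The CV model needs its own calculation once its outcome and expected event count are stated.
2. Penalised (ridge or LASSO) regression on the full candidate list.

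In either case, bootstrap the whole process, including any selection step, and report optimism-corrected AUC and calibration slope as the main performance figures for both models. Keep the statement that external validation is still needed.

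The cost is some extra analysis work and probably software beyond SPSS 23. The reported AUCs will be lower than the apparent ones. No extra patients or measurements are needed.
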